#### **4.1.2 Study population**

##### **4.1.2.1 Inclusion criteria**

Men and women with Idiopathic Parkinson's Syndrome using the UK Brain Bank criteria. (Hughes et al., 1992)(stages 1-3 according to Hoehn & Yahr) with ON medication. (Hoehn and Yahr, 1967), age 30-80 years, any ethnicity, ability to walk without an assistant, Mini-Mental Status Test (MMST)  $\geq 24/30$  (Tombaugh and McIntyre, 1992)Stable dosage of dopaminergic

replacement therapy at least 3 weeks before the start of the study or still without dopaminergic treatment for the duration of the study intervention, written and spoken German.

#### **4.1.2.2 Exclusion criteria**

Concomitant disease(s) (such as malignant diseases, other neurological, orthopaedic, cardiac or psychiatric diseases, major depression, dementia), photosensitivity, non-parkinsonian gait disorder (e.g. due to musculoskeletal symptoms), recent surgery (general and ocular), intraocular implants, strabismus, nystagmus, prominent drooping eyelids, untreated pain, uncorrected visual or auditory impairment that would interfere with training or examinations, Pregnancy, recent deep brain stimulation (THS) or change in parameters of THS within the last year, severe motor fluctuations, initiation of new dopaminergic medication or adjustment of the same within the study period is not provided; In the sense of a real-life setting, this decision is incumbent on the investigator.

Corrective lenses that match the mobile eye tracker are used to correct defective vision.

#### **4.1.2.3 Number of participants and sample size**

For this study, 34 people with Idiopathic Parkinson's Syndrome will be included. Of the 34 people with Parkinson's disease, 17 will be randomised to intervention group 1 and 17 to control group 2.

According to Julious, participants per group are considered a minimum sample size for a pilot study. (Julious, 2005) while Browne specifies a number of participants of 30 for a two-arm study. (Browne, 1995). Therefore, to evaluate the feasibility criteria and preclinical effects of the experimental intervention compared to the conventional control intervention, a sample size of 34 is aimed for, based on 30 participants, including an expected failure rate of 10% and using the formula  $N = n / (1 - (z/100))$ . Here, n is the number of participants (30) and z is the expected failure rate (10%).

#### **4.1.3 Randomisation and concealed allocation**

34 patients with Idiopathic Parkinson's Syndrome will be randomised into one of two groups using a 1:1 allocation ratio. For this purpose, a random number sequence generated by the randomisation software "Sealed Envelope" (<https://www.sealedenvelope.com/>) and sealed opaque envelopes are used. A stratified block randomisation (blocks of 4 and 6) with concealed allocation will be conducted by an independent researcher in the team who will not be involved in participant recruitment, instructions regarding the intervention or testing.

Stratification will be based on only one relevant predictive factor for change in dynamic mobility, namely degree of disability (H & Y stages 1 and 2; 3), due to the small sample size.

#### 4.1.4 Blinding

The raters/test takers of the study will be blinded to the group assignment of the participants, and the participants will be blinded to the study hypotheses.

#### 4.1.5 Unblinding

The planned time of regular unblinding is after completion of the study, specifically after finalisation of the data analysis.

### 4.2 Intervention

#### 4.2.1 Treatment scheme

The study includes a screening, a baseline examination, 16 intervention sessions a' 30 min over 4 weeks, a post-intervention testing, a focus group for the participants of the intervention group and a follow-up call 4 weeks after the end of the intervention.

The duration and number of examinations and treatments (Table 1) will take place in the context of the patients' inpatient interdisciplinary rehabilitation. It is ensured that all study participants receive the same number of treatments in total. In addition, all participants must receive 8 30-min sessions of physiotherapy per week, of which 4 are reserved for the study intervention in group 1 or 2 and represent an additional measure. All therapists will be trained on the study interventions and instructions for participants in both groups and will therefore work according to the same principles.

**Table 1:** Treatment regimen of a (screened possible\*) study participant

| Intervention                | Dosage | Time                                                                      | Duration    |
|-----------------------------|--------|---------------------------------------------------------------------------|-------------|
| Screening*                  | 1x     | After verification of suitability by the investigator and patient consent | 10-15 min   |
| Study inclusion             |        |                                                                           |             |
| Baseline investigation      | 1x     | Day 0 after study inclusion                                               | 75-90 min   |
| Intervention groups 1 and 2 | 16x    | Start on day 1 after the baseline examination                             | 30 min each |

|                          |    |                                                                                                                                           |           |
|--------------------------|----|-------------------------------------------------------------------------------------------------------------------------------------------|-----------|
|                          |    | 4 x per week, 4 weeks in total                                                                                                            |           |
| Postintervention testing | 1x | 4 weeks after the start of the intervention                                                                                               | 75-90 min |
| Focus group              | 1x | 4 weeks after the start of the intervention, only for intervention group 1, at a time interval of >2 hours from post-intervention testing | 45-60 min |
| Follow-up call           | 1x | 4 weeks after end of intervention                                                                                                         | 15 min    |

\*If one or more exclusion criteria are present after screening, the patient will not be included in the study.

#### 4.2.2 Intervention

The intervention is carried out in addition to the therapy units of the inpatient rehabilitation at the Reha Zentrum Münster. All patient goals not addressed by the study intervention as well as neurotherapeutic therapy measures are thus carried out during the usual therapy units (e.g. auditory cueing, cognitive strategies, endurance training, specific posture training).

*Intervention group (Group 1):* Activity-oriented physiotherapeutic training programme with eye movement training; the training is evidence-based and oriented towards guidelines for rehabilitation in idiopathic Parkinson's syndrome (Keus, S. et al., 2014; Grimes et al., 2019; National Institute for Health and Care Excellence (Great Britain), 2017): for 30 min, 4x per week, for 4 weeks, supervised by the respective physiotherapists.

*Control group (group 2):* Activity-oriented physiotherapeutic training programme i. The standard care is evidence-based and oriented towards guidelines for rehabilitation in idiopathic Parkinson's syndrome (Keus, S. et al., 2014; Grimes et al., 2019; National Institute for Health and Care Excellence (Great Britain), 2017): for 30 min, 4x per week, for 4 weeks, supervised by the respective physiotherapists.

The training therefore includes an individualised training adapted to the Hoehn and Yahr stage, which is overall diverse and variable. The training characteristics listed below apply to the training in both intervention groups. The difference between the two groups is only the eye movement training in combination with the exercises described in more detail below.

- Application of the principles of motor learning (external learning focus, repetition, variability, progression, activity-oriented, goal-oriented)
- Specific functional balance training (static and dynamic balance training, e.g. increasingly moving beyond the body's stability limits, secured by the physiotherapist).
- Transfers such as seat-stand
- Functional exercises to improve joint mobility (e.g. trunk rotation with progressive increase to higher body position).
- Functional strength training
- Coordination training
- Fall prevention training
- Training large movement amplitudes with high intensity

The *activity-based physiotherapy training programme with eye movement training (group 1)* will consist of the following elements: An evidence-based routine programme that includes the parameters of motor learning. (Olson et al., 2019), specific functional balance training, improvement of joint mobility, fall prevention and functional independence (Keus, S. et al., 2014) is combined with gaze movement training. The selection of the parameters of gaze movement training was based on various studies that have already investigated gaze movement training in other populations. (Camacho et al., 2019b; Knox and Wolohan, 2015; Matsumoto et al., 2011).. These include the intensity, the practice times for the interventions (in the ON phase) and the distance of the trainee from the wall where a practice poster with a crosshair and different fixation points is placed.

The gaze movement training is intended to direct the focus of the evidence-based activity-oriented routine programme carried out in rehab towards gaze fixation and expansion of saccade amplitude of persons with Idiopathic Parkinson's Syndrome. This means that in addition to physiotherapy exercises to increase coordination, strength and strength endurance, gaze fixation and gaze movement exercises will be trained. These will be based on the parameters of motor learning. (Olson et al., 2019) These exercises are progressively increased using the parameters of motor learning (Olson et al., 2019) and are carried out in combination with the exercises of balance and fall prevention training. The respective physiotherapists receive training to ensure standardised implementation of the intervention. An instructor manual with a collection of exercises is available, which enables individualised tailoring of the exercise programme to the performance level of the participants and still ensures comparability (see Appendix 1 and Appendix 2).

For gaze movement training, an exercise poster with a crosshair and different fixation points is used, which was developed for this clinical study in an interdisciplinary team (see Figure

2a). Using this exercise poster in combination with different exercises for the lower extremity and the trunk, a standardised, individually adapted, progressively increased training programme is then to be carried out over the intervention period. In addition, wall markers are used for eye movement intervention combined with activity-based balance training (Figure 2b). The exercises will be trained in different starting positions (sitting, wide stance, tandem stance, etc.) in order to train different movements in everyday situations. The study participants are accompanied in a 1:1 setting within the framework of individual physiotherapy four times a week. The physiotherapists in charge of each case are available to the participants for questions regarding the training throughout the entire period.

[figure not shown]

**Figure 2a:** Exercise poster

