These findings suggest a positive influence on saccade parameters through targeted eye movement training. Such training potentially also leads to an improved perception of the environment, which could positively influence gait safety and thus reduce the risk of falls.

Neurological physiotherapy for Idiopathic Parkinson's Syndrome at the Reha Zentrum Münster is evidence-based and follows international guidelines for rehabilitation (Keus, S. et al., 2014; Grimes et al., 2019; National Institute for Health and Care Excellence (Great Britain), 2017).. It has not yet been investigated whether additional gaze movement training achieves an additional benefit with regard to the dynamic mobility and fall rate of patients.

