#### **4.4.1.1 Implementation**

The FGA consists of 10 items. The items address walking on a surface without a slope at different speeds, with head turns, with quick turns and stops, climbing stairs and climbing over obstacles. Individual items are scored on a scale of 0-3 points, with 3 points representing the best possible performance of the item. The total score is 30 points. The more points achieved, the better the dynamic balance of the test persons. The duration of the test is 5-20 minutes (Thieme et al., 2009).

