#### Exercise 4: Head flexion and extension in standing position

| Exercise setting      |                                                                                                                                                                                                        | Gaze fixation point                                                                                                        |
|-----------------------|--------------------------------------------------------------------------------------------------------------------------------------------------------------------------------------------------------|----------------------------------------------------------------------------------------------------------------------------|
| Starting position     | Stance: feet hip-width apart on the floor, knees slightly bent                                                                                                                                         | Centre of the crosshairs                                                                                                   |
| End position          | Maximum flexion of the cervical spine

Maximum extension of the cervical spine                                                                                                                   | View towards the triangle (below)

View towards the triangle (above)                                                 |
| Progression options   | I: In addition, raise and lower the arms to 90° (GHG) with the movement.

II: In addition, raise the arms to 90° (GHG) and hold.

III: In addition, raise the arms to 180° (GHG) and hold. | A: View in the direction of the quadrilateral (below & above)

B: View in the direction of the point (below & above) |
| Number of repetitions | 5 x each side; hold each side in the end position for 5 sec.                                                                                                                                           |                                                                                                                            |

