## Exercise 5: Head rotation in standing position

| Exercise setting      |                                                                                                                                                                                                                                                                           | Gaze fixation point                                                                                      |
|-----------------------|---------------------------------------------------------------------------------------------------------------------------------------------------------------------------------------------------------------------------------------------------------------------------|----------------------------------------------------------------------------------------------------------|
| Starting position     | Stance: feet placed hip-width apart on the floor, knees slightly bent                                                                                                                                                                                                     | Centre of the crosshairs                                                                                 |
| End position          | Rotation of the cervical spine to the right

Rotation of the cervical spine to the left                                                                                                                                                                             | View towards the triangle (right)

View towards the triangle (left)                                |
| Progression options   | I: In addition, raise and lower the arms to 90° (GHG) with the movement.

II: In addition, raise and lower the arms with the movement to 90° (GHG) and rotate the torso with it.

III: In addition, raise and lower the arms with the movement to 180° (GHG). | A: View in the direction of the quadrilateral (right & left)

B: View towards point (right & left) |
| Number of repetitions | 5 x each side; hold each side in the end position for 5 sec.                                                                                                                                                                                                              |                                                                                                          |

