## Exercise 4: Diagonal with the arms

| Exercise setting      |                                                                                                                            |
|-----------------------|----------------------------------------------------------------------------------------------------------------------------|
| Starting position     | Stance: Feet placed hip-width apart on the floor, knees slightly bent;
Right or left arm on opposite pelvis (Ex/ADD/IR) |
| End position          | Right or left arm stretched upwards (Flex/ABD/AR)                                                                          |
| Progression options   | I: Knees bent lower
II: Additionally with small dumbbell / weight
III: Standing in tandem                            |
| Number of repetitions | 5 x each direction; hold each for 5 sec. in the end position                                                               |

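### Section 4.2.2 says the arms differ only in eye movement training, but the two instructor manuals also differ in motor content (Exercises 4 and 5, slightly 11, and the start of stepping in 17-20), so an FGA difference cannot be attributed strictly to gaze training alone

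*Protocol*

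**What the plan says.** Section 4.2.2 gives both groups the same dose (30 minutes, four times a week, for four weeks) and a common list of training characteristics. On the contrast between the arms it states: "The difference between the two groups is only the eye movement training in combination with the exercises described in more detail below". Later in the same section, gaze training is presented as an add-on: "in addition to physiotherapy exercises to increase coordination, strength and strength endurance, gaze fixation and gaze movement exercises will be trained". The section refers to an instructor manual with a collection of exercises, which is meant to allow tailoring while keeping the programmes comparable. One manual per group is appended.

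The reason for this contrast is given in section 1.1: "It has not yet been investigated whether additional gaze movement training achieves an additional benefit". The primary endpoint is the FGA, and section 4.4.1.1 describes its content: "The items address walking on a surface without a slope at different speeds, with head turns, with quick turns and stops, climbing stairs".

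**The concern.** If the only difference between the arms is the gaze component, a between-group difference in FGA change can be read as the effect of adding gaze training. That is the question posed in section 1.1. If the motor exercises also differ, the contrast combines gaze training with other changes, and randomisation cannot separate them because they are assigned together.

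The unmatched content bears on the endpoint. Head movement in standing, trunk rotation and stepping are all plausibly related to a walking test that includes head turns and quick turns. Section 5.6.1 also uses the pilot's between-group differences as the basis for sizing a larger trial. An effect labelled as gaze training, but partly due to other tasks, would be carried into that calculation.

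**Working it through.** The plan gives no figure to reproduce here, so the check is a side-by-side reading of Exercises 1-20 (2 warm-up, 18 main part) in the two manuals. It compares starting position, end position and progression, leaving aside the gaze column.

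**Same motor task: Exercises 1, 2, 3, 6-10 and 12-16.** Group 1 adds fixation points to a task that group 2 also performs. Exercises 1 and 2 show that a head movement can be given with fixation points in one arm and without them in the other.

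**Different motor task**

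| Exercise | Group 1 manual | Group 2 manual |
|---|---|---|
| 4 | "Exercise 4: Head flexion and extension in standing position"; levels I-III add arm raising | "Exercise 4: Diagonal with the arms"; level I is a deeper knee bend, then "II: Additionally with small dumbbell / weight", then tandem stance |
| 5 | "Exercise 5: Head rotation in standing position"; torso rotation joins at level II | Upper body and arms rotated from 90° abduction; lunge position at level II |

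Gaze training does not require either substitution, as Exercises 1 and 2 show.

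**Small difference: Exercise 11.** Both arms squat. Only the control manual adds head rotation to the base task.

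**Different start of stepping: Exercises 17-20 (letters Z, M, N, W).** In group 1 the base task is tracing the letter with eyes and head, level I is a lunge stance, and stepping the letter is written only at level III. In group 2 stepping the letter is the base task, and the single progression reverses the sequence. The tracing belongs to the gaze training; the later start of stepping is a separate motor difference.

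**Count**
- Same: 1, 2, 3, 6, 7, 8, 9, 10, 12, 13, 14, 15, 16 = 13; 13/20 = 65%
- Different for no reason linked to gaze training: 4, 5 = 2; 2/20 = 10%
- Small difference: 11 = 1; 1/20 = 5%
- Different start of stepping: 17, 18, 19, 20 = 4; 4/20 = 20%
- Check: 13 + 2 + 1 + 4 = 20

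**Overlap elsewhere**
- Group 1 also has dumbbells (equipment list in the general notes), tandem stand (Exercise 12, level III), torso rotation (Exercise 5, level II) and lunges (for example Exercises 17-20, level I). Only the arm diagonal, as a named task, is missing from its manual.
- Group 2 also moves the head in standing: Exercise 11, Exercises 13 and 14, Exercise 15 at level II and Exercise 16 at level I.
- Both manuals add the same walking training (obstacles, slalom, changes of direction and speed) and stair climbing.

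The cool-down differs too: Exercises 25 and 26, closing and relaxing the eyes, are in the group 1 manual only. These can be read as part of the eye training and are not counted.

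**The case against.** The strongest reply is that the sentence in 4.2.2 is being read too literally. It stands next to a list of shared training characteristics, so it may mean only that both arms share those characteristics and differ in gaze work combined with exercises. With 30 minutes fixed in each arm, some reallocation of content is to be expected. The hypotheses in sections 2.4 and 2.5 already compare one programme with another, the analysis is described as preliminary, and both manuals are printed in full.

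Part of this stands. The tested comparison is at programme level and is unaffected, and the overlap listed above is substantial. But on the looser reading, replacing a standing head movement with an arm diagonal or an upper-body rotation is still not eye movement training, so 'only' remains wrong. A programme-level hypothesis also does not answer the component question in section 1.1.

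A reader might infer three stronger things, none of which the documents support:
- *That six of 20 exercises, or 30% of the training, are confounded.* In four of the six the tracing is the declared gaze component. The share is also of a list from which therapists choose individually, not of training time.
- *That group 1 practises head turns in standing and group 2 does not, so the FGA favours group 1.* Group 2 has standing head movements in Exercises 11 and 13-16, and its earlier stepping could work the other way.
- *That the trial comparison is invalid.* It is a valid randomised comparison of two programmes.

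**Conclusion.** The point holds as an error of description with a limited consequence for interpretation. The clear mismatch is Exercises 4 and 5, with a small one in Exercise 11 and a difference in the start of stepping in Exercises 17-20. A between-group FGA difference would support the programme with gaze training as a package; it could not be attributed strictly to gaze training.

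The effect on the FGA cannot be calculated, in size or direction, because exercises are individualised and the dose of the unmatched tasks is not fixed in advance. The conclusion assumes that therapists deliver the exercises as the manuals describe them. It should be corrected, because the correction is cheap and lets the pilot answer its own question more directly, but it does not undermine the pilot.

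**What to change.** **Before the first patient.** Edit the control manual only, so that Exercises 4, 5 and 11 use the group 1 motor task without fixation points, as Exercises 1 and 2 already do. Leave the group 1 manual unchanged: its Exercise 4 is one of the exercises used for the weekly eye tracking (section 4.4.15). This brings the matched exercises to 13 + 3 = 16 of 20. Then correct 4.2.2, for example: *The groups differ in eye movement training and in Exercises 17-20, where stepping the letter starts at base level in group 2 and at progression III in group 1.* Aligning Exercises 17-20 would change the graded progression; that is a clinical decision and is not required.

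**If enrolment has begun.** Leave the manuals alone. Correct only the sentence in 4.2.2, naming Exercises 4, 5, 11 and 17-20, and limit the conclusion to the two programmes as packages. Summarise the exercises and levels performed in each arm from the existing study diaries. Do this by content and not by number alone, because numbers 4 and 5 mean different tasks in the two arms.

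**Cost.** Low. The first route is a manual edit, one sentence and a note in therapist training. Version 1.1 is dated 27.03.2021 and the first visit was planned for 15.04.2021, which leaves 4 + 15 = 19 days. The second route is one sentence and a table from data already collected. Sample size, visits, endpoints and hypotheses do not change.
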